### Study Setting and Recruitment

The study will recruit patients and their spouses who are interested in the study. The nurse practitioners will inform the researchers of the patients’ interest, and the researchers will explain the research methods and requirements, and the ethical information in detail to the patients. Nurse practitioners from the Oncology Department of the 2 hospitals will screen the eligible patients based on the inclusion criteria and will inform the patients and their spouses about the study. The patients who agree to participate will sign a written informed consent form.

### Participants

#### Inclusion Criteria

##### Patients

The inclusion criteria for patients are as follows: (1) the disease meets the diagnostic criteria of the “Guidelines for Diagnosis and Treatment of Gastric Cancer” [32], the preoperative gastroscopy and pathological diagnosis indicate advanced gastric cancer, and the postoperative pathological classification is type II, III, or IV; (2) age ≥18 years and ability to write and communicate effectively; (3) the main caregiver is their spouse; (4) clear consciousness and no understanding barriers; and (5) written informed consent to participate in this study.

##### Spouses

The inclusion criteria for spouses are as follows: (1) age ≥18 years and ability to write and communicate effectively; (2) the main caregiver is the spouse; (3) clear consciousness and no understanding barriers; and (4) informed consent to participate in this study.

#### Exclusion Criteria

##### Patients

The exclusion criteria for patients are as follows: (1) another diagnosis of gastric cancer or another type of cancer, with severe complications, such as gastrointestinal obstruction and perforation; (2) received or is currently receiving psychotherapy from a psychiatrist or psychologist; (3) cognitive impairment or mental impairment; and (4) severe visual, hearing, and speech impairments.

##### Spouses

The exclusion criteria for spouses are as follows: (1) presence of serious physical diseases or acute diseases, such as cancer, stroke, and cardiovascular or cerebrovascular diseases; (2) received or is currently receiving psychotherapy from a psychiatrist or psychologist; (3) cognitive impairment or mental impairment; and (4) severe visual, hearing, and speech impairments.

### Sample Size

The sample size will be calculated using the following formula for sample size based on the study by Charan and Biswas [33]: sample size = 2 (SD) 2 × (Zα/2 + Zβ)2 / D2. It is based on the FoP-Q-SF (primary outcome) from a previously published study [15]. It showed a 95% power to detect a mean difference of 2.88 points between the control and experimental intervention groups in 61 Chinese patients with breast cancer. Statistical significance will be calculated to achieve a statistical power of 0.9 at a 5% significance level for 70 participants in each group. A 2-tailed test will be used to test the hypothesis. The sample size of each dependent variable is 35. To address dropout, an additional 20% is added to the calculation. As a result, the sample size for the experimental and control groups is 42. Consecutive sampling will be used in this study.

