Researchers, patients with cancer, representatives of patient rights, policymakers, and oncology psychologists from many countries reached an expert consensus, which defined the fear of cancer recurrence as “fears and concerns of patients with cancer regarding possible future cancer recurrence and/or metastasis and/or progression” [9]. The primary manifestations of high-level fear of cancer recurrence have been explained as follows: “highly focused, highly concerned, persistent, hypervigilant of physical symptoms and present for at least 3 months” [10].

The treatment cycle of advanced gastric cancer is long, and the recurrence rate is high. Although the progress of medical technology and the resection rate of advanced gastric cancer have increased, the high postoperative recurrence rate and metastatic rate, as adverse life events, have a tremendous psychological impact on patients [11]. Adverse reactions, such as nausea, vomiting, dry mouth, constipation, and bone marrow suppression, aggravate the psychological burden of patients, making them more fearful of the recurrence and progression of the disease [12].

Several studies [12-14] showed that the level of fear of cancer recurrence (as measured by the Fear of Progression Questionnaire-Short Form [FoP-Q-SF]) among patients with gastric cancer (120-170 cases) was middle to high (score of 35.43-42.3 points), the physical health dimension score was 18.09 (SD 4.52), and the social family dimension score was 17.34 (SD 6.34). The scores of the fear of cancer recurrence were higher in patients with gastric cancer than in patients with breast cancer [15] and early-stage prostate cancer [16]. A previous study [17] found that Chinese patients with gastric cancer have less knowledge of the fear of cancer recurrence. High levels of fear of cancer recurrence seriously affect the health of patients with gastric cancer, resulting in a series of dysfunctional behaviors, including avoidance behavior, hypervigilance of symptoms, and inability to plan for the future, which can reduce quality of life, and at the same time, the unmet supportive needs of cancer patients can lead to lower treatment compliance. These effects can persist for months or even years after treatment, and in severe cases, they can lead to anxiety disorders, posttraumatic stress symptoms, and depression [18].

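### The stated 0.9 power rests on an FoP-Q-SF standard deviation of about 3.7, whereas the protocol's own gastric cancer figures imply at least 7.8

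*Protocol article*

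**What the plan says.** The Sample Size section uses the formula for two independent means, "sample size = 2 (SD) 2 × (Zα/2 + Zβ)2 / D2", and bases it on the FoP-Q-SF, the primary outcome. The only difference it gives comes from an earlier breast cancer study of 61 patients: "It showed a 95% power to detect a mean difference of 2.88 points between the control and experimental intervention groups". For this trial it claims to "achieve a statistical power of 0.9 at a 5% significance level for 70 participants in each group", and adds: "A 2-tailed test will be used to test the hypothesis". Then: "The sample size of each dependent variable is 35". And: "To address dropout, an additional 20% is added to the calculation", which leads to 42 per group. The SD that went into the formula is not given.

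The Introduction reports FoP-Q-SF scores from gastric cancer patients, with totals of 35.43 to 42.3. For the two dimensions, "the physical health dimension score was 18.09 (SD 4.52), and the social family dimension score was 17.34 (SD 6.34").

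Under Instruments and Measures, the patient scale is described as one-dimensional, with a Cronbach alpha of 0.886. The Data Analysis section plans a two-way repeated-measures ANOVA over baseline and two follow-ups. No within-patient correlation is stated anywhere.

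**The concern.** Every input to the formula is given except the SD, so the SD can be solved for. The result is smaller than the SD of either single dimension in the gastric cancer data that the same article quotes. A total score built from two parts of one fear scale should vary more than each part, not less.

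The 0.9 power claim therefore does not hold for the population being enrolled, on the document's own figures. A reader who trusts the claim could take a non-significant result as good evidence that the intervention does nothing, when a true 2.88-point benefit could easily have been missed. The article's Conclusion makes hospital implementation depend on whether the intervention proves effective, so the reading of a null result matters.

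**Working it through.** **Inputs.** From Sample Size: D = 2.88, power 0.9, two-sided 5%, n = 35 per group. From the Introduction: dimension SDs 4.52 and 6.34. Normal quantiles: 1.960 + 1.282 = 3.2415 before rounding. Two quantities are assumptions, because the documents do not give them: the correlation between dimensions (c) and the correlation between visits (r).

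**1. The plan's own figures.** Without an SD, 35 cannot be reproduced forwards. The later steps can: 35 × 1.2 = 42, and 35 patients plus 35 spouses make 70 participants. Solving the formula for the SD:

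- n = 35: SD = 2.88 × √(35/2) / 3.2415 = 12.05 / 3.2415 = **3.72**
- n = 70 patients: SD = 2.88 × √(70/2) / 3.2415 = 17.04 / 3.2415 = **5.26**

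**2. SD of the total score in gastric cancer.** The dimension means add to 18.09 + 17.34 = 35.43, exactly the lower quoted total, so the two dimensions make up the total. Then SD² = 4.52² + 6.34² + 2c × 4.52 × 6.34 = 60.63 + 57.31c.

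- c = 0: √60.63 = 7.79
- c = 0.3: √77.82 = 8.82
- c = 0.5: √89.28 = 9.45
- c = 1: √117.94 = 10.86

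An SD of 3.72 would need c = (13.81 − 60.63) / 57.31 = −0.82, and 5.26 would need −0.58. Strong negative correlations do not fit a scale described as one-dimensional with alpha 0.886.

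**3. Power for 2.88 points with the formula's comparison** (two groups, unadjusted, noncentral t):

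| Patients per group | SD 7.79 | SD 8.82 | SD 9.45 |
|---|---|---|---|
| 35 | 33% | 27% | 24% |
| 42 (no dropout) | 39% | 32% | 28% |
| 70 | 58% | 48% | 43% |

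The difference detectable with 90% power at 35 per group is 3.2415 × SD / √17.5, which is 6.0 points at SD 7.79 and 7.3 at SD 9.45.

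**4. Power for a repeated-measures contrast.** Take each patient's mean of the two follow-ups minus baseline, with equal SDs and equal correlation r between visits. Its variance is SD² × [(1 + r)/2 + 1 − 2r] = SD² × 1.5(1 − r). If 2.88 is the group difference in this contrast, then at 35 per group:

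| r | Contrast SD (total SD 7.79 / 9.45) | Power |
|---|---|---|
| 0.5 | 6.74 / 8.18 | 42% / 31% |
| 0.7 | 5.22 / 6.34 | 62% / 47% |
| 0.8 | 4.26 / 5.18 | 80% / 63% |

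Power of 90% is reached at r of about 0.85 (SD 7.79) to 0.90 (SD 9.45).

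**The case against.** Five points can be made for the plan.

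- **The SD fits its source.** If the cited study had 95% power for 2.88 points, the same formula gives 2.88 × √(30.5/2) / 3.605 = 3.12 with 61 patients in total, and 2.88 × √(61/2) / 3.605 = 4.41 with 61 per group. These bracket 3.72. So a reader might infer an arithmetic error, but the documents do not show one. The problem is that a small SD was carried into a population for which the article itself reports larger ones. Nor is leaving the SD out of a condensed article a fault in itself.
- **The planned analysis is not the formula's test.** This stands. A reader might infer that the trial simply has 24-33% power, but that holds only for the unadjusted comparison. The article also describes psychological indicators as stable, which suggests some within-patient correlation. It gives no value, and at 35 per group the shortfall remains up to r of about 0.85.
- **The 70 and the 2.88 are open to interpretation.** The text does not say outright that 2.88 is this trial's target, but it offers no other difference. Reading 70 as patients conflicts with 42 enrolled per hospital, and unadjusted power would still be only 43-58%.
- **Recruitment may exceed the plan.** The Results section reports 97 couples. Split evenly with no loss, that is about 48 per hospital. Unadjusted power would be about 32-43%, and the contrast at r = 0.8 would give about 77-91%. Only the most favourable corner reaches 90%, and a 20% loss would leave about 38 per group.
- **No passage says a null result will be read as no effect.** True. That harm is a foreseeable misreading, not a stated intention.

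**Conclusion.** The point holds. The 0.9 power claim is not supported by the gastric cancer figures in the same article. The formula needs an SD of about 3.7 (5.3 on the less likely reading of 70), while those figures imply about 7.8 to 9.4 for a between-dimension correlation of 0 to 0.5, and at least 7.8 for any non-negative correlation. At 35 per group, power for 2.88 points is about 24-33% with the protocol's own formula. With the repeated-measures contrast it is about 31-80% for between-visit correlations of 0.5 to 0.8.

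That power falls short of 0.9 is firm unless the correlation between visits is about 0.85 or higher. The exact percentages are less firm. They depend on the two assumed correlations, on equal SDs across visits, and on 2.88 being the target.

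A reader might also infer that the trial must be enlarged. That does not follow: what needs correcting is the statement of what the design can detect.

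**What to change.** Rewrite the Sample Size paragraph so that it:

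1. states the SD used, its source and any assumed within-patient correlation;
2. says that 2.88 points is the target difference and that 35 means patients per group, with 70 counting spouses, if that is what is meant;
3. replaces the 0.9 claim with the power and detectable difference for the planned analysis, using the gastric cancer SDs and shown over a range of correlations;
4. says that a non-significant result will be interpreted from its confidence interval.

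Possible wording for item 3: *With 35 evaluable patients per group and a total-score SD of 7.8 to 9.4 (assuming a between-dimension correlation of 0 to 0.5), power for 2.88 points is about 24-33% for an unadjusted comparison, for which the difference detectable with 90% power is about 6 to 7 points. For the change from baseline to the mean of the two follow-ups, power is about 31-80% at assumed between-visit correlations of 0.5 to 0.8.* If the sponsor holds a documented SD or correlation for this population, those values should replace the assumed ones.

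The cost is one paragraph and a less favourable stated power. No extra patients are needed.

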### Data Analysis

Statistical analysis will be conducted using IBM SPSS 21.0 (IBM Corp). The level of statistical significance will be set as α=.05. Descriptive statistics will be used to describe the sociodemographic and psychosocial variables, including percentages, means, and standard deviations. For comparing the baseline characteristics of the 2 groups, the Student *t* test or Mann-Whitney *U* test will be used for quantitative variables and the chi-square test will be used for categorical variables. Two-way repeated-measures ANOVA will be performed to determine the presence of a significant change in the fear of cancer recurrence and DCI in the intervention and control groups in order to analyze the effects of the intervention and compare the control group with the experimental group at baseline and 2 and 4 months postintervention. This analysis will be performed on an intention-to-treat basis. A *P*-value of <.05 will be considered statistically significant for differences between the 2 groups.

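### The stated 0.9 power comes from a formula for one two-group comparison of means and does not refer to the planned three-visit repeated-measures ANOVA, for which 0.9 is not assured

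*Protocol article*

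**What the plan says.** The Sample Size section of the protocol article gives the formula "sample size = 2 (SD) 2 × (Zα/2 + Zβ)2 / D2". It takes its effect from a breast cancer study described as having "95% power to detect a mean difference of 2.88 points between the control and experimental intervention groups". The target is to "achieve a statistical power of 0.9 at a 5% significance level", and "A 2-tailed test will be used to test the hypothesis". It then states "The sample size of each dependent variable is 35" and adds 20% for dropout to reach 42 per group. It gives no SD, no correlation between visits and no pattern of effect over time.

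The Data Analysis section plans a different kind of test: "Two-way repeated-measures ANOVA will be performed to determine the presence of a significant change in the fear of cancer recurrence and DCI", covering baseline, 2 months and 4 months. Its decision rule is that a P-value below .05 "will be considered statistically significant for differences between the 2 groups". It does not say whether the group term, the group-by-time term or a comparison at one visit decides.

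**The concern.** The formula applies to one contrast with one degree of freedom: a difference D between two independent groups, measured once. It has no term for repeated visits, their correlation or an interaction. The planned ANOVA offers two terms that could show a treatment effect, and neither is that contrast. The group-by-time term tests the effect with 2 degrees of freedom, and its power depends on r and on when the effect appears. The group term averages the group difference over all three visits, including baseline, where the intervention cannot yet have acted.

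The stated 0.9 is therefore attached to a test that the analysis section does not name as deciding. A reader of a null FoP-Q-SF result would take it as a negative finding with 90% power, without knowing whether that holds for the test performed.

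**Working it through.** **Inputs from the Sample Size section.** Power 0.9, two-sided 5%, D = 2.88, and 35 per group before dropout. I read 35 as the number per group because 35 × 1.2 = 42. The same section also says "for 70 participants in each group"; that conflict is a separate point.

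**Reproducing the plan's figure.** With no SD given, 35 at 0.9 cannot be derived independently. Solving the formula backwards:

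- d = (1.960 + 1.2816) × √(2/35) = 0.775, which for D = 2.88 means SD = 2.88/0.775 ≈ 3.72.
- (n/2)d² = 17.5 × 0.775² ≈ 10.51.
- The formula then returns 0.900 at 35 per group. The corresponding unadjusted t test gives 0.89.

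This d favours the plan, because it makes the plan's own formula exactly right.

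**Assumptions.** Equal variances, equal correlation r between any two visits, no baseline difference, and 35 couples per group analysed. There are three effect patterns over baseline, 2 and 4 months: building (0, d/2, d), full at 2 months (0, d, d) and late (0, 0, d). The building pattern is plausible because the 2-month visit follows only the second of four sessions (Outcome Assessment).

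**Group-by-time term**, non-central F on 2 and 136 df, with λ = (n/2) × Σ(δₜ − mean δ)² / (1 − r):

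- Building: Σ = 0.5d², so λ = 5.25/(1 − r).
- Full or late: Σ = (2/3)d², so λ = 7.01/(1 − r).

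**Group term**, non-central F on 1 and 68 df, with λ = (n/2) × (mean δ)² × 3/(1 + 2r):

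- Building: mean = d/2, so λ = 7.88/(1 + 2r).
- Full: mean = 2d/3, so λ = 14.01/(1 + 2r).
- Late: mean = d/3, so λ = 3.50/(1 + 2r).

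**4-month difference adjusted for baseline score**, 1 and 67 df: λ = 10.51/(1 − r²).

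| Test (35 per group, d = 0.775) | r = 0.3 | r = 0.5 | r = 0.7 |
|---|---|---|---|
| Group-by-time, building | 0.68 | 0.83 | 0.97 |
| Group-by-time, full or late | 0.81 | 0.92 | 0.99 |
| Group term, building | 0.59 | 0.50 | 0.43 |
| Group term, full | 0.83 | 0.74 | 0.66 |
| Group term, late | 0.31 | 0.26 | 0.22 |
| 4-month, baseline-adjusted | 0.92 | 0.96 | 0.99 |

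The group-by-time term reaches 0.9 at r ≈ 0.59 (building) or r ≈ 0.46 (full or late). Over r = 0.3 to 0.8 the group term never exceeds 0.83.

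**If nobody drops out (42 per group).** At r = 0.5 the group-by-time term has power 0.89 (building) or 0.96 (full or late). The group term reaches at most 0.89, at r = 0.3 with a full effect.

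**The case against.** A reader might infer from the table that the trial is underpowered. The documents do not support that. In a pretest-posttest design with an analysis aimed at change, group-by-time is the natural deciding term, and at moderate to high r it meets or exceeds 0.9. The section on developing the intervention describes psychological indicators as stable over frequent assessments. That is not a correlation estimate, but it points towards higher r. The lowest figures belong to the group term, which the protocol never names as deciding.

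Four further objections have weight:

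- The d of 0.775 is not stated in the plan; it is back-solved.
- The Data Analysis sentence could be read as including comparisons at each visit, and the 4-month one would be close to what the formula sizes. Even so, the unadjusted 4-month t test gives 0.89, so only the baseline-adjusted version clears 0.9.
- Naming the deciding term is often left to an analysis plan, so its absence alone is not a fault.
- Sizing with a two-means formula and analysing with repeated measures is a common simplification.

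These objections limit the point but do not remove it. The article states both a power and a test, and the power was not calculated for that test. The simplification would be harmless if the simple contrast were named as primary, or if it were known to be conservative. The first is not done. The second fails at r = 0.3 for every pattern, and at r = 0.5 for a building effect.

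**Conclusion.** The point holds as a mismatch: the 0.9 belongs to a single comparison of two means, not to the planned ANOVA. At the implied effect and 35 per group, the group-by-time term has power from 0.68 to 0.99 over r = 0.3 to 0.7, depending on when the effect appears. If the group term were used to decide, it would stay below 0.9 for r = 0.3 to 0.8 because it averages in baseline. So 0.9 is not assured, and it is equally not shown to be missed.

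The figures rest on a back-solved d and on an assumed r and effect pattern, none of which the plan gives. The mismatch itself rests on none of them; it follows from reading the two sections side by side.

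**What to change.** **Preferred.** In Data Analysis, name the between-group difference in patient FoP-Q-SF at 4 months, adjusted for the baseline score, as the primary test, with the ANOVA group-by-time term as supportive. In Sample Size, say that the formula refers to this 4-month comparison. With the same couples and the implied effect, its power is 0.92 at r = 0.3 and 0.96 at r = 0.5.

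**Alternative.** Keep the ANOVA, name group-by-time as the deciding term, and replace 0.9 with its power under a stated SD, r and effect pattern.

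**Cost.** One or two sentences in each section, no additional couples and no new measurements. Under the preferred option the 2-month visit becomes supportive; under the alternative the stated power may be less favourable. The two hospitals are non-equivalent groups, so baseline adjustment aligns the test with the power statement but does not remove confounding by hospital. If baseline means differ, it can also give a different answer from a change-score analysis. The change from baseline to 4 months should therefore be reported as a sensitivity analysis.

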## Results

The research activities for this study commenced in October 2022. Participant recruitment and data collection began in February 2023, with the expectation of completion within 12 months (by December 2024). As of October 30, 2023, a total of 97 gastric cancer patients and their spouses have been recruited, and all baseline data have been collected. Once sufficient participants are recruited, subsequent measures will be performed and data analysis will commence. The primary results of this study are anticipated to be announced in June 2024.

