### Limitations

This study has some minor limitations. First, this study involves a long-term intervention, and some participants may not complete the study owing to loss of follow-up or physical deterioration during treatment. Second, missing data may influence the results and must be addressed statistically. To overcome this bias, a 20% attrition rate will be included in the sample size calculation, and an intention-to-treat analysis will be performed during the data analysis. Finally, this study will only include patients during chemotherapy.

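### The 42 per group is 35 plus 20%, which does not keep 35 evaluable patients at the plan's own 20% attrition rate; the 70 in the same paragraph also needs defining

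*Protocol article*

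**What the plan says.** All references are to the protocol article.

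- **Sample Size, formula and inputs.** The formula is "sample size = 2 (SD) 2 × (Zα/2 + Zβ)2 / D2". The test is two-sided. The difference is taken from an earlier breast cancer study: "It showed a 95% power to detect a mean difference of 2.88 points between the control and experimental intervention groups". No standard deviation is printed.
- **Sample Size, power.** The calculation is said "to achieve a statistical power of 0.9 at a 5% significance level for 70 participants in each group".
- **Sample Size, base and inflation.** "The sample size of each dependent variable is 35. To address dropout, an additional 20% is added to the calculation". The result is 42 for each group.
- **Limitations.** To deal with missing data, "a 20% attrition rate will be included in the sample size calculation".
- **Methodology and Design.** Each hospital recruits 42 patients together with their spouses, and each hospital is one group.
- **Hypotheses.** The word participants covers patients and spouses together.
- **Outcome Assessment.** The primary outcome is the patient's FoP-Q-SF score. The partner's score is secondary.
- **Results.** By 30 October 2023, "a total of 97 gastric cancer patients and their spouses have been recruited, and all baseline data have been collected".

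**The concern.** There are two matters, of unequal weight.

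The first is arithmetic. An attrition rate is a share of those enrolled, so the enrolled number must be the evaluable number divided by one minus that rate. Adding the rate to the evaluable number gives too few. The plan adds, and so misses its own target of 35 if its own dropout assumption comes true. What is at stake is whether the stated size, power and attrition rate agree with one another.

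The second is clarity. Power of 0.9 is attached to 70 in each group, but enrolment is built on 35, and the paragraph does not say how the two numbers relate. The primary outcome has one value per couple, the patient's, so the reader needs to know how many patients per group the formula returned. Without the standard deviation, that cannot be worked out from the text.

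**Working it through.** **Inputs.** Base 35, 20% added, final 42, two-sided α = 0.05, power 0.90 and D = 2.88 are from Sample Size. The meaning of the 20% is from Limitations. The recruitment unit is from Methodology and Design.

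**1. Reproduce the plan's figure.** 35 × (1 + 0.20) = 42. This matches.

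**2. Apply the plan's attrition rate to it.** 42 × (1 − 0.20) = 33.6, so 33 or 34 evaluable patients per group, against 35 wanted.

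**3. Dropout that 42 does cover.** 1 − 35/42 = 0.167, or 16.7%.

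**4. Inflation that matches a 20% attrition rate.** 35/(1 − 0.20) = 43.75, rounded up to 44 per group, or 88 couples in total. Check: 44 × 0.8 = 35.2.

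**5. Cost in power.** Assume that 35 per group gives exactly 90% power on the plan's formula. The standard deviation and D then cancel, and for m per group

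power = Φ[(1.960 + 1.282) × √(m/35) − 1.960].

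| Evaluable per group | Power |
|---|---|
| 35 | 90.0% |
| 34 | 89.2% |
| 33 | 88.2% |

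**6. What 70 could mean.** Solving the plan's formula for the standard deviation, SD = D × √(n/2) / (1.960 + 1.282), with D = 2.88:

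- n = 35 per group implies SD = 3.72.
- n = 70 per group implies SD = 5.26.

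So 35 and 70 cannot both be the number of patients per group from one calculation. Two other readings fit the remaining figures:

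- **Persons per group.** 35 patients + 35 spouses = 70, and 70 × 1.2 = 84 persons = 42 couples, which is what each hospital is to recruit.
- **Patients in total.** 2 × 35 = 70, in which case the words placing 70 in each group are a slip.

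The two standard deviations are back-solved from the sample sizes. They show what each reading would require and are not evidence for either.

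**The case against.** **The effect is slight.** The shortfall is 44 − 42 = 2 couples per group and about 1 to 2 percentage points of power. Recruitment has also passed 88 in total if the 97 counts couples. That stands, and it makes this a matter of correct reporting more than a threat to the trial. It does not make 42 right. The split of the 97 by hospital is not given, so it is not known whether each group has reached 44.

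**The 20% could be a plain margin.** Read alone, Sample Size only says that 20% was added, and that is what was done. But Limitations names the figure as an attrition rate, and at that rate 42 falls short.

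**A reader might infer an outright contradiction**, with 70 and 35 both given as the per-group size for the same power. The documents do not support that. Power of 0.9 is attached only to the 70. The 35 is given per dependent variable, with no power of its own. Because Hypotheses counts spouses as participants, 70 persons and 35 couples can describe the same sample.

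**A reader might also infer that counting spouses doubles the apparent information**, or that 42 enrolled would leave less than half of what is needed. Neither follows. Enrolment is built on 35, and each hospital recruits 42 patients with their spouses in addition, so no spouse takes a patient's place. The less-than-half figure requires 70 to be patients per group, the reading that fits Methodology and Design worst.

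**Conclusion.** The dropout arithmetic is wrong on the article's own figures. An enrolment of 42 per group does not retain 35 at 20% attrition; it covers 16.7%. The consequence is 33 to 34 evaluable patients per group and about 88% to 89% power instead of 90%. The power figures assume that 35 is the patient number which gives 90% on the plan's formula, and the article does not show this because it states no standard deviation. The shortfall in numbers needs no such assumption.

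The relation of 70 to 35 is unclear wording and not a demonstrated contradiction. It still needs correcting, because a reader cannot tell which number the formula returned for the primary outcome. If 70 counts persons, the power statement includes spouses, who have no primary outcome value. If 70 is the total, the reference to each group is wrong.

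**What to change.** In Sample Size, make one of these two changes:

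- State 35/0.8 = 43.75, rounded up to 44 couples per group (88 in total), for 20% attrition, and bring the 42 in the Abstract and in Methodology and Design into line; or
- Keep 42 and state that it allows for 16.7% attrition, or that at 20% attrition power is about 88% to 89%. Amend Limitations to match.

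In the same paragraph, state the number of patients per group that the formula gave for the patient's FoP-Q-SF score, with the standard deviation used. State also whether 70 means persons (patients plus spouses) per group or patients in total. Only the authors can settle this; the text does not decide it.

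The cost is a rewording. With 97 already reported, the first option needs no further recruitment if that figure counts couples and each hospital has at least 44. The authors should report the split by hospital to show this.
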